#### Traditional Mediterranean diet (TM)

The TM arm is based on the dietary patterns described in the Prevention with Mediterranean Diet study^(10)^ (∼50–60 % of energy CHO; ∼15 % energy protein; ∼25–35 % energy fat) with a focus on olive oil, nuts, seafood, wholegrains, fruit and vegetables. Recommendations for red meat and whole-fat dairy products will be in line with the Australian Guide to Healthy Eating, and red wine (optional) will be in line with the National Health and Medical Research Council Australian alcohol guidelines (2020) of two standard drinks or less per day and at least two alcohol free days per week. This is a deviation from TM diets to align with the Australian alcohol guidelines.

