#### Lower carbohydrate diet (LC)

The LC dietary intervention will focus on whole foods whilst following an LC dietary pattern including wholegrains, some fruits and vegetables. Whole-fat dairy products, red meats and eggs will be included, whilst olive oil, seafood and nuts will not be encouraged, as a point of difference from the Mediterranean arms. The macronutrient distribution targets will be the same as those of the LCM dietary intervention (∼35 % energy CHO; ∼20 % energy protein; ∼45 % energy fat)^(26,27)^.

Similarities and differences between diets are briefly summarised in Tables 1 and 2.

**Table 1. tbl1:** Macronutrient composition of intervention diets Table 1 long description.

	Traditional Mediterranean	Lower carbohydrate Mediterranean	Lower carbohydrate
Carbohydrates (%TE)	∼50–60 %	∼35 %	∼35 %
Protein (%TE)	∼15 %	∼20 % (more from white meat, legumes, etc.)	∼20 %
Fat (%TE)	∼25–35 %	∼45 % (more from olive oil, nuts, fish, etc.)	∼45 %

%TE, percent total energy.

**Table 2. tbl2:** Similarities between intervention diets Table 2 long description.

Traditional Mediterranean	Lower carbohydrate Mediterranean	Lower carbohydrate
	35:20:45	35:20:45
Wholegrains	Wholegrains	Wholegrains
Whole-fat dairy products	Whole-fat dairy products	Whole-fat dairy products
Fish/legumes/nuts	Fish/legumes/nuts	
Olive oil	Olive oil	
≤ 2 standard drinks/d	≤ 2 standard drinks/d	≤ 2 standard drinks/d

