### Adherence and dietary assessment

Prior to the intervention, a diet history interview will be conducted by an Accredited Practising Dietitian face-to-face or by telehealth with participants to capture habitual dietary pattern information. This assessment will serve as a baseline of habitual intake and will be used to tailor intervention advice as per participants’ dietary preferences.

A 4-d weighed food record (three weekdays and one weekend day) will be requested at weeks 3 and 8 of the trial to determine adherence to the diet intervention. Participants will be informed of the requirement; however, they will not be told in which weeks these assessments will occur to reduce the risk of pre-planning or intentional modification of intake (bias). Weighed food record data will be collected using the *Australian Easy Diet Diary* (Xyris Software (Australia) Pty Ltd) app for iOS and Android smartphones and tablets, and participants will be instructed on its use during the baseline dietary consults. Participants also complete a checklist of weekly food group targets achieved.

The Mediterranean Diet Adherence Screener (MEDAS)^(33)^ will be used at baseline, week 3, week 8 and week 12 to ensure that both Mediterranean diet arms are routinely following the guidelines of the Mediterranean diet. The MEDAS is also completed for participants in the LC diet arm to maintain consistency and monitor that there is an adequate point of difference between interventions. Compliance with the LC interventions (CHO 35 
±
 10 % energy) will be assessed using the two weighed food records and weekly checklists/Easy Diet Diary data.

Dietary satisfaction has been linked to long-term diet adherence^(34)^. The Diet Satisfaction-45 survey^(35)^ will be used as a measure of satisfaction pre- and post-intervention. This tool explores changes in dietary satisfaction between the habitual dietary pattern and satisfaction with the randomised dietary arm. In addition, the Theory of Planned Behaviour survey^(36)^, which monitors participants’ attitudes toward the dietary intervention and their willingness to change at different time points, will be completed prior to the intervention diet start.

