### Statistical analysis

186 (62 per group) participants were calculated using a 5 % significance level with a variance and change of 0·2 in the MetS-Z score after a 12-week cardioprotective diet and exercise programme by Hickman *et al*.^(47)^ based on 80 % power with G*Power software^(48)^ for our parallel RCT design. A total of 222 participants will be recruited to account for 20 % drop out. Final data will be analysed using intention-to-treat analyses with a linear mixed model (SPSS, IBM), and covariates (age, weight loss) will be added to the model if required in consultation with a biostatistician. Data will be coded and remain blinded to outcome assessors until all analyses are completed. Statistical significance will be considered as a *p* value
<
 0·05.

In addition, a per-protocol secondary analysis will be conducted. Compliance with the LC interventions (CHO 35 
±
 10 % energy) will be assessed using the two weighed food records and weekly checklists/Easy Diet Diary data. Mediterranean diet adherence will be estimated using average of the MEDAS scores across the study, weekly checklists/Easy Diet Diary data and weighed food records, that is, overall, attaining high consumption of monounsaturated fatty acids; daily consumption of fruits, vegetables, whole grains, fibre, weekly consumption of fish, poultry, nuts and legumes; a relatively low consumption of red meat; and moderate consumption of alcohol^(49)^. MEDAS scores of 8 or above in the Mediterranean arms, which is considered moderate adherence in most studies/trials^(50)^, will be included in the analysis.

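### The per-protocol rule does not keep the pre-diet MEDAS score out of the adherence average, and it sets no carbohydrate criterion for the traditional Mediterranean arm

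*Protocol article*

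**What the plan says.** All references are to the protocol article.

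- **Timing.** Under Adherence and dietary assessment, MEDAS "will be used at baseline, week 3, week 8 and week 12". It is also completed in the LC arm, to "monitor that there is an adequate point of difference between interventions".
- **Mediterranean adherence.** Under Statistical analysis, "Mediterranean diet adherence will be estimated using average of the MEDAS scores across the study", together with "weekly checklists/Easy Diet Diary data and weighed food records, that is, overall, attaining high consumption of monounsaturated fatty acids" and a list of further food groups. The inclusion threshold is "MEDAS scores of 8 or above in the Mediterranean arms". No numeric limit is attached to the checklists, diary or food records.
- **Carbohydrate adherence.** The same section begins the carbohydrate rule with "Compliance with the LC interventions (CHO 35" and completes it as ± 10 % of energy, judged from the two weighed food records and the checklist or diary data. The rule names the LC interventions, that is, LC and LCM.
- **Diet definitions.** Traditional Mediterranean diet (TM) and Table 1 put TM at about "50–60 % of energy CHO". LC and LCM are both at about 35 %. Under Lower carbohydrate diet (LC), "olive oil, seafood and nuts will not be encouraged, as a point of difference from the Mediterranean arms".

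**The concern.** A per-protocol analysis is meant to compare the diets as they were followed. Two features of the rule work against that.

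First, a score taken before the diet starts describes habitual eating, not adherence. If it enters the average, the hurdle depends on where a person began, and two people who eat identically on the intervention can be classified differently. This would act in TM and LCM but not in LC, which has no MEDAS hurdle.

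Second, carbohydrate share is the main designed difference between TM and LCM, yet the numeric rule for TM does not refer to it. Someone allocated to TM who ate a lower carbohydrate Mediterranean diet would stay in the TM per-protocol set, which blurs the comparison of the combined diet with the traditional one.

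**Working it through.** The plan gives no computed figure for the per-protocol rule, so there is none to reproduce. The inputs are the four MEDAS time points, the cut-off of 8, the band of 35 ± 10 % and the TM target of about 50–60 %. I take the cut-off to apply to the average.

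**1. Baseline in the average.** Let b be the baseline score and m the mean of weeks 3, 8 and 12. On the literal reading:

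(b + 3m)/4 ≥ 8, so b + 3m ≥ 32, so m ≥ (32 − b)/3.

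| Baseline b | On-diet mean needed |
|---|---|
| 4 | 28/3 = 9.33 |
| 5 | 27/3 = 9.00 |
| 6 | 26/3 = 8.67 |
| 7 | 25/3 = 8.33 |
| 8 | 24/3 = 8.00 |
| 10 | 22/3 = 7.33 |

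With weeks 3, 8 and 12 only, the requirement is 8.0 for everyone.

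- Scores 4, 9, 9, 9: 31/4 = 7.75. Excluded, although every on-diet score passes.
- Scores 10, 7, 7, 8: 32/4 = 8.0. Included, although the on-diet mean is 22/3 = 7.33.

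**2. Which error matters.** The documents give no MEDAS distribution, so this step is an illustration under assumptions: baseline mean 4 to 7, on-diet mean 8 to 10, between-person and within-person SD 1.3 each, and scores rounded and held within 0 to 14. Percentages are of a whole Mediterranean arm.

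| Baseline mean | On-diet mean | On-diet average ≥ 8 | Four-point average ≥ 8 | Adherent on diet but excluded | Not adherent but included |
|---|---|---|---|---|---|
| 4 | 9 | 78.1 % | 46.6 % | 31.5 % | 0.0 % |
| 5 | 9 | 78.1 % | 53.4 % | 24.7 % | 0.0 % |
| 6 | 9 | 77.8 % | 60.1 % | 17.8 % | 0.0 % |
| 7 | 8 | 54.4 % | 46.5 % | 9.0 % | 1.2 % |

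Across all the combinations run, wrongful exclusion ranged from about 9 % to 32 %, and wrongful inclusion was at most about 1 %.

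**3. Numeric criteria by arm.**

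| Arm | Carbohydrate target | Carbohydrate criterion | MEDAS criterion |
|---|---|---|---|
| TM | about 50–60 % | none | ≥ 8 |
| LCM | about 35 % | 35 ± 10 % | ≥ 8 |
| LC | about 35 % | 35 ± 10 % | none |

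The band is 35 − 10 = 25 % to 35 + 10 = 45 % if ± 10 % means percentage points of energy. If it is relative, 0.1 × 35 = 3.5, and the band is 31.5–38.5 %. A TM participant with MEDAS 9 and 40 % carbohydrate is 10 points below the lower end of the TM range, yet meets the TM rule and, on the absolute reading, the LCM rule as well. On the relative reading 40 % falls outside the band, but the same overlap arises at 35 %. The overlap narrows and does not disappear.

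**The case against.** **Baseline.** The average is described as a measure of adherence, and nobody can adhere to a diet not yet begun. The authors may well intend the on-diet visits only, and an SAP that is not shown may say so. This stands as far as it goes: the article never states that baseline is included. But it does fix a summary over the whole study with four scheduled scores, and an analyst following the words would include all four. A reader might infer that baseline is definitely averaged in; the text supports only the literal reading, not the intention.

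**Other sources for TM.** Mediterranean adherence also draws on checklists, diary data and food records, so MEDAS is not the only evidence. That is correct. However, the pattern they are judged against is a list of foods and fat type, with no carbohydrate share. LCM also keeps whole grains and vegetables, so the list does not separate the two diets.

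**Unequal hurdles.** A reader might infer that two criteria for LCM against one elsewhere is itself a defect, and that it favours LCM. The documents do not support this. LCM combines two patterns, so adherence to it naturally means meeting both. No pass rates are given from which retention by arm could be worked out, and the direction of any bias is not shown.

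**LC participants with a high MEDAS.** It is tempting to say they must be excluded. The LC section says only that olive oil, seafood and nuts are not encouraged, and MEDAS in LC is for monitoring. Someone scoring 8 or more there has broken no stated instruction.

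**Conclusion.** The point holds in two parts, both confined to a secondary analysis.

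- **MEDAS average.** Conditional on the literal reading, the required on-diet mean varies from 9.33 at a baseline of 4 to 7.33 at a baseline of 10. The practical harm is the loss of adherent participants who began furthest from the diet: roughly 9–32 % of a Mediterranean arm under the assumed distributions. Admission of non-adherent participants is negligible under the same assumptions. The arithmetic is exact; the percentages are only illustrative.
- **TM carbohydrate.** This follows from the text without assumptions about data. TM has no carbohydrate criterion, so per-protocol TM and LCM can overlap. The width of the overlap depends on whether ± 10 % is absolute (25–45 %) or relative (31.5–38.5 %). How many participants would fall there cannot be estimated from the article.

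The intention-to-treat primary analysis is not touched.

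**What to change.** Amend the per-protocol definition before unblinding:

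1. Average MEDAS over weeks 3, 8 and 12 only.
2. State whether ± 10 % is in percentage points of energy or relative to 35 %.
3. For per-protocol TM, also require mean carbohydrate from the two weighed food records to lie above the LC band: above 45 % of energy on the absolute reading.
4. Report the number excluded in each arm and by which criterion.
5. Report MEDAS in the LC arm. Exclude LC participants scoring 8 or more only in a sensitivity analysis.

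All the data are already scheduled, so the cost is wording. The downside is a somewhat smaller TM per-protocol set, and the added TM criterion is itself a selection made after randomisation, which is why the exclusions need to be visible by arm. If on-diet averaging was always intended, one clause settles item 1; the TM criterion is still needed.

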## Discussion

The Mediterranean dietary pattern and LC dietary patterns are popular diet approaches for cardiometabolic health. To the authors’ knowledge, this study will be the first of its kind to evaluate two popular dietary approaches, the TM and an LC dietary pattern against a combined LCM dietary pattern for people with the MetS. The study is novel in its approach as previous studies have only compared the LCM to a TM diet and the American Diabetes Association diet^(27)^ or a low-fat diet^(28)^. By comparing all three dietary approaches, this study will ascertain which diet has the greatest benefit in reducing MetS severity (a combination of cardiovascular and diabetes risk factors) and provide an opportunity to begin exploring the dietary factors that may contribute to greater improvements in cardiometabolic health. This is also the first dietary trial to evaluate the change in MetS severity using the MetS-Z score.

The Mediterranean dietary pattern has been shown to be feasible and well adhered to in Australian RCT^(51,52)^, whereas the LC has shown mixed adherence in studies^(22,53,54)^. However, the feasibility of these diets in the free-living general population is unknown. This study will also add to the limited body of literature on the LCM diet by furthering our understanding of its feasibility and acceptability among individuals with MetS within an Australian cohort. Combining these approaches provides a dietary strategy that can be easily adapted and implemented in clinical practice.

Limitations of this study include the self-reported dietary intakes, which are inherently biased. To combat this, a combination of measurement methods including weighed food records, dietary consults, MEDAS and checklists will be used, which, when combined, will provide a measure of both actual and habitual dietary intake to capture less common food sources. Another limitation of this trial is that the diets are not laboratory controlled as foods are not provided to participants throughout, which can lead to poor implementation and adherence to the prescribed diets. Instead, participants are provided with general dietary guidance and will be required to implement this in a free-living setting. This approach was designed to more closely reflect real-world conditions to assess the feasibility of these diet patterns in Australia and to increase the generalisability of the study outcomes. It is hypothesised that the individualised dietary consultations with participants and accompanying resources will help participants achieve dietary patterns that are sustainable. Due to the nature of the dietary advice and resources provided, it will also not be possible to blind participants to their intervention allocation. However, data will be coded and remain blinded to outcome assessors until all analyses are completed.

In summary, the benefits of the Mediterranean diet approach for cardiovascular health are well-established. The evidence-based benefits of an LC eating pattern are emerging, particularly in trials for people who are overweight/obese and/or have T2D. This study will build on prior research and test whether the combined effect of an LCM dietary pattern has greater benefits for MetS-Z and cardiometabolic health in adults with MetS. By evaluating the LCM against the ‘gold standard’^(55)^ TM diet and LC approaches, this study represents a pioneering investigation in Australia aimed at identifying dietary factors that effectively enhance metabolic and cardiometabolic health.

## Appendix 1

1. What was your main motivation for deciding to join the Effects of Dietary Approaches on Metabolic Syndrome study?
2. What aspects of your dietary approach did you like or find enjoyable?
3. What aspects of your dietary approach did you dislike or find unenjoyable?
  - Prompt: How did you deal with this?
4. Do you see yourself following this dietary approach now that you have finished the study?
  - If yes, is there anything you would change going forward?
  - If no, prompt why?
5. How well do you think you were able to follow the dietary recommendations provided to you?
6. Could you please comment on the support given to you during the study?
  - Prompt: Enough support? Not enough support? Format? Person? Frequency?
7. How did your family and friends react to you following the dietary approach?
8. How did this diet compare to some you’ve tried in the past, if any?
9. What are some changes to your health, if any, you’ve noticed over the intervention period?
10. What were some other health changes you’ve made influenced by the study during the 12-week period?
11. Is there any other feedback you would like to provide about your experience in the study?

## Fig. 1 Long description

The table is structured with columns for Enrolment, Allocation, and Post-allocation activities across 12 weeks. It includes rows for Recruitment, Interventions, and Assessments. Recruitment activities include Eligibility screen and Informed consent at the enrolment stage, and Randomisation at the allocation stage. Interventions include Mediterranean, Lower carbohydrate, and Lower carbohydrate plus Mediterranean diets, each spanning different weeks. Assessments include MetS severity, DEXA, Blood measures, Anthropometry, Non-invasive cardiovascular assessments, Dietary consults, Weighed food record, Diet interview, and Adverse monitoring, each scheduled at specific weeks. The table provides a clear timeline for each activity, showing when they start and end.

Navigate back to Fig. 1.

## Table 1 Long description

A table comparing the macronutrient composition of different diets. The table has three columns and four rows, including the header row. The columns are labeled Traditional Mediterranean, Lower carbohydrate Mediterranean, and Lower carbohydrate. The rows are labeled Carbohydrates (%TE), Protein (%TE), and Fat (%TE). Row 1: Carbohydrates (%TE), Traditional Mediterranean, ~50-60 percent, Lower carbohydrate Mediterranean, ~35 percent, Lower carbohydrate, ~35 percent. Row 2: Protein (%TE), Traditional Mediterranean, ~15 percent, Lower carbohydrate Mediterranean, ~20 percent (more from white meat, legumes, etc.), Lower carbohydrate, ~20 percent. Row 3: Fat (%TE), Traditional Mediterranean, ~25-35 percent, Lower carbohydrate Mediterranean, ~45 percent (more from olive oil, nuts, fish, etc.), Lower carbohydrate, ~45 percent.

Navigate back to Table 1.

## Table 2 Long description

A table comparing three different diets: Traditional Mediterranean, Lower carbohydrate Mediterranean, and Lower carbohydrate. The table has three columns and five rows, including the header row. The columns are labeled Traditional Mediterranean, Lower carbohydrate Mediterranean, and Lower carbohydrate. The rows include macronutrient ratios, types of foods, and alcohol consumption guidelines. Row 1: Macronutrient ratios: 35:20:45 for both Traditional Mediterranean and Lower carbohydrate Mediterranean, and 35:20:45 for Lower carbohydrate. Row 2: Whole grains are included in all three diets. Row 3: Whole-fat dairy products are included in all three diets. Row 4: Fish, legumes, and nuts are included in all three diets. Row 5: Olive oil is included in all three diets. Row 6: Alcohol consumption is limited to less than or equal to 2 standard drinks per day for all three diets.

Navigate back to Table 2.
